**Fig. 1 Fig1:**
[figure not shown]
Flowchart of recruitment and observation procedures of this study. 1 m, 3 m,6 m, and 12 m means 1 month, 3 months, 6 months, and 12 months after Conbercept treatment

### Participants and recruitment

More than 5000 patients will be recruited from 43 ophthalmic centers in china that suffer from AMD, PCV, and PM (List of Ophthalmic Center in Additional file 3). And it is the first time for them to receive ocular injection of Conbercept. Doctors in outpatient clinic who diagnose and prescribe are independent of the investigators in this study. The 43 ophthalmic centers cover most regions of China. The recruitment capacity of each center will be mainly depended on the daily outpatient and registration capacity, as well as follow-up conditions. Participation is voluntary and consent is obtained before the procedures. Until now, the recruitment and primary pharmacogenomic analysis is ongoing and 3055 patients have been recruited.

### Inclusion criteria:

Age ≥ 18 years;Patients are diagnosed as AMD, PCV and CNV secondary to PM;Patients will receive intravitreal injection of Conbercept;Patients are willing to have a long-term follow–up in the clinical center;Signed consent form.

### Exclusion criteria:

Participate in other interventional therapy at the same time;Received anti-VEGF treatment (including intravitreal injection or systematic application) within three months prior to enrollment.

### Data collection and management

Investigators in the 43 ophthalmic centers should follow Standard Operating Procedures (SOPs) during clinical data and blood sample collection, data recording and transfer, sample storing and transfer. All of the data will be filled in the electronic case report form (CRF). At the initial visit (V1), information about the participant’s sex, age, body weight, height, vital signs, medical/surgical history, concomitant medications and eye conditions will be recorded. For ETDRS vision, eye examinations, optical coherence tomography (OCT), fluorescein fundus angiography (FFA) will be checked by clinicians who have got international unified certification. The eye conditions, treatment records, accompanying medications and adverse events are recorded by practiced clinicians at five visits. Clinical images will be uniformly transferred to Shanghai Jiaotong University Ophthalmic Reading Center and evaluated by qualified graders. The specific items are listed in Table 1.

**Table 1 Tab1:** Assessment protocol for the current study from V1 to V5

Visit of data entry	V1	V2	V3	V4	V5
Meets enrollment / exclusion criteria	X				
Month		1	3	6	12
Days		30 (± 7) days after first injection	90 (± 7) days after first injection	180 (± 7) days after first injection	360 (± 7) days after first injection
Consent form	X				
Demographic data	X				
Systemic and ocular disease history	X				
Best corrected visual acuity	X	X	X	X	X
Optical coherence tomography	X	X	X	X	X
Accompanying medication	X	X	X	X	X
Data record	X	X	X	X	X
Treatment program records		X	X	X	X
Adverse events	X	X	X	X	X

The clinical data and fundus imaging data will be uploaded to Electronic Data Capture (EDC) System called Oracle Clinical and Oracle Remote Data Capture (OC/RDC) churned out according SOPs. The EDC system has been checked by third party and meets international standard. And data from different centers will be managed together and go through logistic check. Each modification trace can be recorded to make sure the data is real and reliable.

Patients’ blood samples will be collected in coagulation-promoting tubes (8 ml) and EDTA procoagulant tubes (8 ml), and then be centrifuged for 20 min at 4000 rpm to separate serum and plasma respectively. All the samples will be send to Ophthalmic Biobank of Shanghai Jiaotong University via cold-chain logistic and then stored at − 80 °C.

### Main outcome measures

#### Primary outcome

The primary outcome is visual changes primarily recorded as best-corrected visual acuity (BCVA) in EDTRS letters at V2, V3, V4, and V5 minus baseline vision (V1). The efficacy was graded as significantly effective (visual improvement ≥15 letters in EDTRS); effective (visual improvement ≥5 letters and < 15 letters in EDTRS); invalid (visual improvement < 5 letters and visual reduction< 5 letters in EDTRS); deterioration (visual reduction≥5 letters in EDTRS) [15]. Moreover, patients graded as significantly effective and effective that is BCVA improvement≥5 letters in EDTRS are defined as having response to Conbercept treatment and the response rate (the rate of patients graded as significantly effective and effective) will be assessed in the whole study population and in each diseases.

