Among subjects, 500 patients will be selected to conduct pharmacometabolomics analysis compared with 500 healthy volunteers for detecting disease-associated metabolites. After the evaluation of patients’ curative parameters (listed below), preliminary pharmacogenomics and pharmacometabolomics analysis will be carried out. We will pick up 500 patients, half of them have good response from significant effective group and half have no response from deterioration group, their blood samples will be analyzed by pharmacogenomics and pharmacometabolomics to find out response-associated predictors, and then the predictors of patients’ response to Conbercept will be further validated in all of the recruited subjects. Figure 1 is the study design flow.

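### Any gain of 5 or more letters counts as response to Conbercept, even after the study eye has received another CNV treatment, and the omics groups are drawn from the same grades

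*Protocol article*

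**What the plan says.** All references are to the protocol article.

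- **Primary outcome.** Visual acuity change is the value at V2, V3, V4 and V5 minus V1. Four grades follow: *significantly effective* (gain of at least 15 letters), *effective* (gain of 5 to under 15), *invalid* (change under 5 either way) and *deterioration* (loss of at least 5). The top two grades together are the responders: "BCVA improvement≥5 letters in EDTRS are defined as having response to Conbercept treatment". The response rate is reported overall and by disease.
- **Study design and objectives.** For the omics analysis 500 patients are chosen: "half of them have good response from significant effective group and half have no response from deterioration group". Then "the predictors of patients’ response to Conbercept will be further validated in all of the recruited subjects". No visit is named for the grading that forms these groups.
- **Participants and recruitment.** "Doctors in outpatient clinic who diagnose and prescribe are independent of the investigators in this study".
- **Exclusion criteria.** "Participate in other interventional therapy at the same time" is an exclusion. Table 1 marks eligibility at V1 only.
- **Table 1.** The row "Treatment program records X X X X" covers V2 to V5, and accompanying medication is recorded at every visit. No section links these records to the grading.
- **Secondary outcome.** Response-related factors are examined after 3 months of treatment.

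**The concern.** The label names a drug, but the rule looks only at letters. A patient who does poorly on Conbercept by month 3, then receives another CNV treatment in the study eye and stands 5 letters above baseline at month 6 or 12, is by definition a Conbercept responder. At 15 letters the same patient qualifies for the good-response side of the omics comparison, which is meant to find predictors of response to this drug.

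The article expects some patients to respond poorly or not at all (Background and Discussion). These are the patients most likely to be moved to something else, so the error tends to turn failures into responders. If switch or add-on practice differs between AMD, PCV and myopic CNV, it would also distort the comparison of response rates between diseases.

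**Working it through.** **No figure to reproduce.** The article gives no expected response rate, standard deviation or rate of other treatment. The size below rests on assumptions.

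**Inputs from the article.** Response at a gain of at least 5 letters; top grade at 15 or more; deterioration at a loss of 5 or more; 250 patients per omics group; target of more than 5000 patients; loss to follow-up below 20%, so about 5000 × 0.8 = 4000 or more at month 12.

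**Assumed inputs.** Normal change from baseline, mean 5 or 8 letters at both V3 and V5; SD 13 at V3 and 14 at V5; V3–V5 correlation 0.7. Of patients with a V3 gain under 5, 5%, 10%, 20% or 30% switch. The other treatment adds 5 or 8 letters by V5.

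**Share who switch.** P(V3 gain < 5) is 0.50 for mean 5, and Φ((5 − 8)/13) = 0.409 for mean 8. The share of all patients who switch therefore runs from 0.05 × 0.409 = 2.0% to 0.30 × 0.50 = 15%.

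**Three month-12 rates.** Let D be the V5 change without the other treatment, S = 1 for switched patients, and a the letters added.

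- A, as written: P(D + aS ≥ 5)
- B, same patients without the added letters: P(D ≥ 5). This is 50.0% for mean 5 and Φ(3/14) = 58.5% for mean 8.
- C, every switched patient counted as a non-responder: P(D + aS ≥ 5 and S = 0)

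A − B is the response produced by the other treatment. A − C also includes switched patients who would have reached 5 letters anyway. Simulation results for selected scenarios:

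| Mean; switch probability; added letters | Switched, % of all | A | B | C | A − B | A − C | B − C | Top-grade pool there only because of the other treatment |
|---|---|---|---|---|---|---|---|---|
| 8; 5%; 5 | 2.0 | 58.8 | 58.5 | 57.9 | 0.3 | 0.9 | 0.6 | 0.6% |
| 5; 20%; 5 | 10.0 | 51.6 | 50.0 | 47.5 | 1.6 | 4.1 | 2.5 | 3.0% |
| 5; 20%; 8 | 10.0 | 52.6 | 50.0 | 47.5 | 2.6 | 5.1 | 2.5 | 5.6% |
| 5; 30%; 8 | 15.0 | 53.9 | 50.0 | 46.2 | 3.9 | 7.7 | 3.8 | 8.2% |

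The first and last rows give the smallest and largest values over all 16 combinations for A − B, A − C and the last column. B − C runs from 0.6 to 3.8 points.

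**Against sampling error.** The standard error of a rate near 50% is √(0.25/4000) = 0.79 points, or √(0.25/5000) = 0.71 points. An inflation of 0.3 points is below one standard error. At 10% switching, 1.6–2.6 points is about two to three.

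**Omics groups.** If 250 patients are drawn from the V5 top grade, 0.6–8% is about 250 × 0.006 = 1.5 to 250 × 0.08 = 20 patients. For illustration, take an assumed marker frequency of 40% in true responders and 27% in non-responders, with two-sided α = 0.05. A fraction m of misplaced patients gives an observed frequency of 0.40(1 − m) + 0.27m. Power falls from 87% (m = 0) to 84% (m = 5%) and 80% (m = 10%).

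**The case against.** **The article is silent and the full protocol may settle it.** It cites a full protocol, version 2.0, that is not shown, and a rule for events during follow-up often sits there or in the analysis plan. That limits the point, but does not remove it. The definition of a responder is fixed in the article with no condition on treatment, so any such rule would have to change that definition.

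**Grading vision as observed is legitimate in a real-world cohort.** This stands. It is a treatment-policy rate and should be kept. What it does not support is the name response to Conbercept, or its use to find predictors specific to that drug.

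**Existing provisions might cover it.** The exclusion of other concurrent therapy could be read as lasting through follow-up, but no section withdraws or regrades a patient who starts such therapy later. Propensity matching and weighting (Data analysis) are offered for confounding in general and leave the label unchanged.

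**Four stronger readings are tempting and are not supported.**

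- That the inflation is the full 0.9–7.7 points of A − C. Part of that gap is patients who would have responded anyway.
- That every switched patient should simply count as a non-responder. That rule undershoots the no-switch rate by 0.6–3.8 points, an error as large as the one it removes or larger in the 5-letter scenarios.
- That the article documents switching. It places photodynamic therapy among earlier treatments and describes other anti-VEGF drugs as having emerged and been studied. It does not say that study patients move to them. Cataract surgery is not mentioned at all and was not modelled.
- That the omics groups are certainly contaminated. The grading visit is not named. At month 3, the path of failing by V3 and then switching contributes nothing.

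**Conclusion.** The point holds in a limited form. As written, the rule attributes to Conbercept any qualifying gain made after another CNV treatment to the study eye, and the omics good-response group inherits that attribution. On assumed switching of 2–15% and an added 5–8 letters, the month-12 response rate is inflated by about 0.3–4 points, and about 0.6–8% of the month-12 top grade is there only because of the other treatment. At low switching the effect is within sampling error; at about 10% it is not. The true size is unknown because the article gives no switch rate. The omics effect shrinks or vanishes if grouping uses month 3. This is worth correcting in the definitions; it does not invalidate the as-observed results.

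**What to change.** **Primary outcome.** Keep the as-observed response rate, but describe it as response under a strategy that starts with Conbercept. Report beside it, overall and by disease, the rate of response while on Conbercept without other CNV treatment to the study eye, and the number of patients who received such treatment.

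**Study design and objectives.** Name the visit at which grades form the omics groups, for example month 3, in line with the secondary outcome on response-related factors. Patients with other CNV treatment to the study eye before that visit are not eligible for the good-response group. Those who still deteriorated may stay in the no-response group, with a sensitivity analysis that leaves them out. Removing them outright would discard clear failures: in the simulation, switched patients make up about 2–18% of the month-12 deterioration pool.

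**Cost.** Wording only, since treatment records and accompanying medication are already collected during follow-up. The downside is a second, somewhat lower response rate to explain and a slightly smaller good-response pool.

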#### Secondary outcome

The changes of retinal edema will be evaluated by central fovea retinal thickness (CRT in μm) at V2, V3, V4 and V5.The different therapeutic regimens of Conbercept prescribed by doctors and applied on different diseases in real-world clinical practice will be assessed, including number of treatments, frequency of injection (times per year), interval time (months).Response-related factors for Conbercept to macular neovascular diseases after 3 months’ treatment will be examined. We will compare the macular leakage area (mm^2^) and the CNV area (mm^2^) to baseline in FFA between patients who response to Conbercept treatment and patients with no response, and their relationship with the responders and nonreponders will be further analyzed.The potential biomarker of patients’ response to Conbercept will be investigated by pharmacogenomics and pharmacometabolomics as mentioned above in study design. The genomic variation between patients who respond to Conbercept treatment and patients who have no response to Conbercept drug treatment will be detected. Conbercept-sensitive associated Single Nucleotide Variations (SNVs) will be picked out by comparing the data of single nucleotide polymorphisms dbSNP and hapMap Database to remove common single nucleotide polymorphisms (SNPs) or SNVs information. Then we will design gene panel based on Next Generation Sequencing to validate the Conbercept-sensitive genomic regions among the whole study population. Besides, prediction model will establish to figure out Conbercept-sensitive genotype in macular neovascular diseases. For pharmacometabolomics studies, blood samples of patients and healthy volunteers will be analyzed by mass spectrometry to primarily screen disease-associated metabolites. The associations of genotype and metabolites with clinical endpoint will be assessed and further validated in the whole study population. Those signatures (gene/ metabolites) will be considered to be predictors of patients who will possibly have good response to Conbercept treatment, and those in non-responders will be recognized as potential predictors of patients who do not respond to Conbercept. Finally, we will build an Oracle database about macular neovascular diseases based on clinical information, pharmacogenomics, and pharmacometabolomics.Safety data: adverse events (AE) and severe adverse events (SAE) were defined according to other large-scale clinical trial on intravitreal injection of anti-VEGF drugs [14–16]. AE and SAE need to be recorded, and their relevance to drug or procedures will be estimated. The number and percentage of AE and SAE in the whole study population and in each disease will be calculated.

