**Methods:**

This study is a multicenter, prospective, observational study of Conbecept treating macular neovascular diseases in China. Patients suffered from age-related macular degeneration, polypoidal choroidal vasculopathy, and pathological myopia who already planned to receive Conbercept treatment will be recruited. We aimed to enroll more than 5000 patients from 43 ophthalmic centers in China. Patients’ clinical data and blood samples will be collected during the one-year follow-up period. Finally, the safety and efficacy of Conbercept, and the potential predictors of patients’ response to Conbercept will be investigated by pharmacogenomics and pharmacometabolomics analysis.

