Although the above clinical trial results showed that Conbercept had good efficacy and safety in treating AMD [14], the exact therapeutic regimen and the efficacy still needs to be further studied in real world. The reasons are as follows: i) Limitation of external validity of randomized controlled trials (RCTs) conducted in AMD, because they may not fully reflect the clinical application of Conbercept in real world; ii) Lack of RCT of Conbercept in the treatment of CNV secondary to PM, and the efficacy of Conbercept in PCV only resulted from subgroup analysis. Therefore, further clinical trials of Conbercept in other macular neovascular disease need to be explored, and our study may provide the preliminary evidence for further RCTs in PM and PCV; iii) Anti-VEGF therapy poses significant financial and treatment burden on patients and social insurance system due to frequent injections and visits. Moreover, some patients have poor or even no response to the drugs. It is important to find out those who have good response and develop individualized therapeutic regimen with the use of pharmacogenomics and pharmacometabolomics technologies.

Therefore, we present the design and methodology of a prospective study to investigate the efficacy and safety data of Conbercept in treating macular neovascular disease in clinical practice and explore the relationships of phenotype and the effectiveness of the Conbercept through pharmogenomics and pharmacometabolomics in China.

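### With every patient on Conbercept and no comparator, the planned analyses can find markers of visual outcome under treatment, but not markers of drug sensitivity, non-response or high benefit

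*Protocol article*

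**What the plan says.** All references are to the protocol article.

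- **Design.** The abstract's Methods state: "This study is a multicenter, prospective, observational study of Conbecept treating macular neovascular diseases in China". No comparator arm is described.
- **Exposure.** Under Inclusion criteria: "Patients will receive intravitreal injection of Conbercept". Under Exclusion criteria: "Participate in other interventional therapy at the same time". No group with the disease on another treatment, or on none, is described.
- **Controls.** Study design and objectives has 500 patients "compared with 500 healthy volunteers for detecting disease-associated metabolites". Data analysis uses biobank healthy controls to look for disease biomarkers.
- **Response.** Under Primary outcome, patients who gain 5 letters or more from their own baseline "are defined as having response to Conbercept treatment". A loss of 5 letters or more is graded as deterioration.
- **Marker discovery and validation.** Study design and objectives selects 500 patients: "half of them have good response from significant effective group and half have no response from deterioration group". The predictors are then validated in all recruited subjects. Data analysis sets the selection cutoff at p < 0.05.
- **Interpretation.** Secondary outcome looks for Conbercept-sensitive variants and a Conbercept-sensitive genotype. Of the signatures, it says that "those in non-responders will be recognized as potential predictors of patients who do not respond to Conbercept". Data analysis adds the aim of finding a high-benefit population.
- **PCV and PM.** Background says "our study may provide the preliminary evidence for further RCTs in PM and PCV". The Discussion speaks of high-level evidence and, later, of convincing evidence.

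**The concern.** A patient's change under treatment is the sum of the change that would have occurred anyway and the change the drug adds. The article itself describes these diseases as causing severe, irreversible vision loss. A patient who loses 5 letters on Conbercept might have lost more without it, and a patient who gains might have had a milder course. Neither can be seen here.

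A marker of fast natural progression would therefore collect in the deterioration group and be reported as a marker of drug non-response. The text goes beyond outcome prediction when it speaks of drug sensitivity and high benefit, since benefit is a contrast with not receiving the drug. The abstract and the Discussion link the biomarker work to waste from treating poor responders and to individualised therapy, so readers are likely to take the labels at face value. The only limitation the Discussion names is the absence of other ethnic groups.

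**Working it through.** **1. Can the design separate the two kinds of marker?** The documents give no figure to reproduce here. The question is one of identifiability.

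For patient *i* with marker *M*: change under treatment = natural course(*M*) + drug effect(*M*). Only the sum is observed. Separating the terms needs patients with the disease at another treatment level, so that a marker-by-treatment interaction can be estimated.

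- Treated versus untreated: none, since treatment is an entry criterion.
- Treated versus another drug: no such group is described.
- Healthy volunteers: they do not have the disease, so they carry no information on its untreated course.
- Multivariable models, propensity score matching (PSM) and inverse probability weighting (IPW), from Data analysis: with only treated patients, they supply no untreated or other-drug contrast.
- Validation in all recruits: this is the same treated cohort, so a purely prognostic marker is expected to hold up there too.

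This part needs no assumed number.

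**2. How readily would a purely prognostic marker be selected?**

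From the documents: groups defined by a gain of 15 letters or more and a loss of 5 or more; 250 per group; p < 0.05 (two-sided assumed). The Background gives a mean change of 8.97 letters after three months in the 0.5 mg group of the earlier trial.

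Assumed: normal change with mean 3 to 8.97 and SD 12 to 18 letters; correlation *r* between marker and change of 0.05 to 0.20; identical drug benefit in everyone, so there is no drug sensitivity to find.

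Formulas, with a = (15 − mean)/SD and b = (−5 − mean)/SD:

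- Gap between group means, in SD of change = φ(a)/[1 − Φ(a)] + φ(b)/Φ(b)
- Marker difference, in SD of marker, d = *r* × gap
- Selection probability ≈ Φ(d × √(250/2) − 1.96)

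Example, mean 5 and SD 15: a = 0.667, b = −0.667, gap = 1.265 + 1.265 = 2.53. With *r* = 0.10, d = 0.253; 0.253 × 11.18 = 2.83; Φ(2.83 − 1.96) = 0.81.

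| SD of change | Gap (SD) | r = 0.05 | r = 0.10 | r = 0.20 |
|---|---|---|---|---|
| 12 | 2.79–2.80 | 0.34–0.35 | 0.88 | >0.99 |
| 15 | 2.53–2.54 | 0.29–0.30 | 0.81 | >0.99 |
| 18 | 2.36–2.37 | 0.26 | 0.75–0.76 | >0.99 |

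The assumed mean hardly matters; *r* and the SD do.

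**3. The same check with a carrier marker.** Assume 30% carriers, an overall mean of 8.97, and a natural course 3 letters worse in carriers (means 6.87 and 9.87), with equal drug benefit. At SD 15, the chance of a gain of 15 or more is 0.294 in carriers and 0.366 in non-carriers. The chance of a loss of 5 or more is 0.214 and 0.161.

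- Carrier share among large gainers: 0.3 × 0.294 / (0.3 × 0.294 + 0.7 × 0.366) = 25.6%
- Carrier share among deteriorated: 0.3 × 0.214 / (0.3 × 0.214 + 0.7 × 0.161) = 36.4%

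With 250 v 250, the selection probability is 74% (95% at SD 12, 53% at SD 18). For a 2-letter shift it is 67%, 41% and 27% at SD 12, 15 and 18. For a 5-letter shift it is 100%, 99% and 92%. Testing the 5-letter response rate in 1,500 carriers v 3,500 non-carriers, taken on its own, gives 0.82 to 1.00 across these cases. Validation would therefore usually confirm the marker.

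**4. Can the label point the wrong way?** Assumed values, SD 15:

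| | Untreated change | Drug adds | Treated mean | Gain ≥5 | Loss ≥5 |
|---|---|---|---|---|---|
| Carriers | −12 | +15 | +3 | 44.7% | 29.7% |
| Non-carriers | −1 | +10 | +9 | 60.5% | 17.5% |

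Carriers gain more from the drug, yet would be reported as the non-responding genotype. This shows that reversal is possible, not that it is likely.

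**The case against.** The best defence is that response is an operational label. Primary outcome defines it as a gain of at least 5 letters, and Secondary outcome speaks of associating genotype and metabolites with the clinical endpoint. Read this way, a predictor of response is a predictor of outcome under Conbercept, which the design can deliver. The text also hedges (potential predictors, possibly a good response), and the aim is secondary and exploratory. This softens the point. But hedging expresses doubt about whether an association is real, not about what it means if real, and drug sensitivity and high benefit go beyond the operational label.

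Several further points stand in part:

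- Responders and non-responders are compared within each disease, so prognostic differences between diseases do not drive those comparisons. Differences within a disease remain.
- Retinal thickness, leakage area and neovascular area are also assessed. They too are observed only under treatment.
- The number, frequency and interval of injections vary and are recorded. Doctors choose them, so that variation is open to confounding, and no marker-by-intensity contrast is described.
- Non-responders in the sense of Primary outcome include patients with little change, whereas discovery uses only the deterioration group.
- The Discussion sentence on convincing evidence goes on to say that the data may benefit further randomised trials. High-level evidence is the clearer conflict with the Background.

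A reader might infer that the protocol intends to withhold Conbercept from marker-defined patients. It does not say so: the stated use is to help doctors treat patients effectively and to individualise therapy. A reader might also take the selection probabilities as the chance of mislabelling. They are only the power to detect a real association with outcome, under chosen inputs.

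**Conclusion.** The point holds as one of interpretation. The single-arm design is legitimate for describing routine care and for predicting visual outcome under Conbercept. It cannot show that a marker identifies sensitivity to the drug, failure to respond to it, or high benefit, and the listed adjustment methods and same-cohort validation do not change that. This conclusion rests on the article's stated design and on no assumed number.

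The size is illustrative only. Under the normal model above, with no effect of the marker on drug benefit, selection probability runs from about 0.3 (*r* = 0.05) through 0.75–0.88 (*r* = 0.10) to above 0.99 (*r* = 0.20). The SD, the correlation and the shift in natural course are not in the documents. Separately, the Discussion's claims for PCV and PM are stronger than the Background's preliminary evidence.

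**What to change.** - In Study design and objectives, Secondary outcome and Data analysis, define the signatures as markers associated with visual outcome under Conbercept. Replace the terms Conbercept-sensitive, predictors of patients who do not respond, and high-benefit population accordingly.
- State as a limitation that, without a comparator, the study draws no conclusion on who benefits or fails to benefit from the drug.
- In the Discussion, bring the high-level and convincing evidence claims for PCV and PM into line with the Background: preliminary evidence for further randomised trials.

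The cost is a more modest claim. No new data, procedures or analyses are needed. A drug-specific claim would need a comparable group with the disease that is untreated or on another treatment, and a marker-by-treatment interaction test. That would be a different study and is not asked for here.

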### Quality control and management

We have made SOPs, videos and OC/RDC system to train all staffs involved in this study how to collect data, and deal with blood sample. The apparatus applied to our study have been certificated by CFDA. All prescribed drugs are from hospital pharmacy, and the empty bottle of Conbercept after injection will be retrieved to ensure the dosage used.

Data Management: Clinical information should be timely, accurately and completely recorded and entered into the CRF on national network of EDC, maintaining confidentiality in accordance with the local law for data protection. The electronic CRF should be consistent with the original medical records. All adverse events, concomitant medications should be documented, serious adverse events should be reported to the relevant authorities within 24 h.

Follow-up management: Follow-up should be conducted according to required time point under the rules. The investigators should enroll in local patients or patients who plan to have regular and long-term follow-up in the hospital, and the rate of lost to follow-up should be controlled below 20%. These procedures would help to minimize possible bias.

Center management: All researchers will be checked for the qualification, and then be trained to make sure they are familiar with the study protocol and will carry out the study strictly. Each center should appoint a clinical research coordinator (CRC) for quality control, making sure the CRF form timely recorded, assisting the check and inspection, drug reception, storage, distribution and checking procedures. CRC should report to PI when they found abnormal data or non-compliances to the protocol.

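### Per-disease AE/SAE percentages can mix injection exposure with per-injection risk; rates per injection and per patient-year should stand beside them

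*Protocol article*

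**What the plan says.** The safety item under Secondary outcome in the Protocol article has two parts. Events are recorded and judged for cause: "AE and SAE need to be recorded, and their relevance to drug or procedures will be estimated". They are then summarised: "The number and percentage of AE and SAE in the whole study population and in each disease will be calculated". No denominator and no time at risk is given.

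The same section makes the regimen an outcome in its own right: "The different therapeutic regimens of Conbercept prescribed by doctors and applied on different diseases in real-world clinical practice will be assessed". Number, frequency and interval of injections are listed there. The protocol therefore does not fix exposure, and it allows for exposure to differ by disease.

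Follow-up runs to a last visit at "360 (± 7) days after first injection" (Table 1). Under Quality control and management, "the rate of lost to follow-up should be controlled below 20"%.

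The Data analysis section says that all data will be tested. It assigns chi-square or Fisher's exact tests to categorical data across groups, and lists logistic and Cox models, propensity score matching and inverse probability weighting. None of these is tied to adverse events, injection counts or follow-up time.

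**The concern.** An event caused by the injection procedure can arise at each injection. If one disease is injected more often than another, more of its patients will have had such an event by month 12, even when each injection is equally safe. The per-disease percentage does not separate the two explanations.

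This matters because safety is a stated aim, and the Discussion presents the study as evidence for PCV and for CNV secondary to pathological myopia, where use is off-label. A disease that receives fewer injections could look safer for that reason alone. The general testing clause in Data analysis could also be applied to these percentages and return a small p-value that reflects treatment intensity.

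**Working it through.** **There is no plan figure to reproduce.** The article gives no adverse event rate, no expected injection count by disease and no safety power calculation. Everything below is illustration under stated assumptions.

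**Inputs from the article:** one year of follow-up; loss to be kept below 20%; more than 5000 patients in total, with no split by disease.

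**Assumed inputs:** per-injection risk r, equal in two diseases, constant and independent between injections; k injections per patient in the year; a given number of patients per disease.

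**Step 1: effect of injection count.** The percentage of patients with at least one injection-related event is 1 − (1 − r)^k.

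| r | k = 3 | k = 6 | ratio 6 v 3 | k = 7 | ratio 7 v 3 |
|---|---|---|---|---|---|
| 0.2% | 0.60% | – | – | 1.39% | 2.3 |
| 0.5% | 1.49% | 2.96% | 1.99 | 3.45% | 2.3 |
| 1% | 2.97% | – | – | 6.79% | 2.3 |
| 2% | 5.88% | 11.42% | 1.94 | – | – |
| 5% | 14.26% | 26.49% | 1.86 | – | – |

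(– means not calculated.) For example, at r = 0.5%, 1 − 0.995^3 = 1.49% and 1 − 0.995^6 = 2.96%.

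The ratio depends mainly on the injection gap and hardly on r. At r = 0.5%, 3 v 4 injections gives 1.49% v 1.99%, a ratio of 1.33, and equal counts give a ratio of 1. A rate per injection would be 5 per 1,000 in both diseases whatever k is.

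**Step 2: would a test notice?** Two-sided 5% comparison of two proportions, 3 v 6 injections, identical per-injection risk:

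| Patients per disease (assumed) | r = 0.5% | r = 2% |
|---|---|---|
| 500 | 35% | 88% |
| 1000 | 61% | 99% |
| 1667 | 82% | >99% |

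The figures are the chance of declaring a difference between diseases.

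**Step 3: effect of loss to follow-up.** Take a true one-year risk I with constant hazard λ = −ln(1 − I), 20% lost, and all enrolled patients in the denominator.

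- Loss spread evenly over the year: observed = 0.8·I + 0.2·[1 − (1 − e^(−λ))/λ]. For I = 10%, λ = 0.105 and the observed figure is 9.02%, a factor of 0.90. For I = 2% the factor is 0.90, and for I = 30% it is 0.91.
- All loss straight after baseline: observed = 0.8·I, a factor of 0.80. This is the extreme case.

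If loss is the same in each disease, the factor is shared and the contrast between diseases is almost unchanged. It distorts the contrast only if loss differs by disease.

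**The case against.** The strongest reply is that the planned measure is legitimate and that no safety comparison between diseases is announced. The percentage of patients with an event is the one-year risk under actual practice, which is what a real-world study should report. If regimens differ by disease, that difference is part of the risk that patients face. The safety sentence says the percentages will be calculated, not compared. The between-disease comparison that the article does name, in the subgroup paragraph of Data analysis, concerns genomic and metabolic signatures. Injection number and interval are reported as a separate outcome, so a reader would see exposure by disease, and events are judged for relation to drug or procedure. Denominators and exposure-adjusted rates are also matters that a full protocol or SAP, not shown here, may settle.

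Most of this stands and limits the point. A reader might infer that the disease percentages measure exposure instead of risk, or that the plan will rank the diseases on safety. The documents support neither: they give no injection counts by disease, and no safety contrast is specified. Nor do they support treating 20% as an expected loss rate. It is a management ceiling, and missed or out-of-window visits go to telephone registration before a visit counts as lost.

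Two things remain. The article does name its safety summary, and that summary is less informative than the design and the collected data allow. The clause that all data will be tested also leaves open a chi-square test of these percentages across diseases. Reporting injections elsewhere does not give a rate of procedure-related events with its uncertainty.

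**Conclusion.** The point holds as a cheap improvement to a valid but incomplete summary. It is not an error that invalidates the safety results.

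If injection counts differ between diseases to the extent assumed (3 v 6 or 3 v 7), percentages of injection-related events would differ about 1.9- to 2.3-fold with no difference in per-injection risk. With similar counts the effect is close to nil. These ratios rest wholly on the assumed injection gap and apply to events that arise from injections. Events unrelated to injection depend on time under observation instead. Loss to follow-up is the smaller matter: about a 10% relative reduction at the ceiling if spread evenly, and a distortion of disease contrasts only if loss is uneven between diseases.

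It might also be inferred that the overall percentage cannot be set beside results from fixed-regimen trials. The article does not show how such trials report their events, so that conclusion is not drawn here.

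**What to change.** In the safety item under Secondary outcome:

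1. Keep the numbers and percentages, and state that the denominator is patients.
2. Add, overall and for each disease, procedure-related events per 1,000 injections and all AE and SAE per 100 patient-years. Give 95% confidence intervals that allow for repeated injections within a patient, for example a Poisson model with log injections (or log follow-up time) as offset and a variance clustered by patient.
3. Show total injections and total follow-up time beside each row.
4. State that any between-disease statement about procedure-related safety will rest on the exposure-adjusted rates.

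Table 1 already schedules adverse events at V1 to V5 and treatment records at V2 to V5, and the first injection is at V1. No new data are needed. The cost is a few extra table columns and a little extra analysis.
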